Comparative study of EMLA cream and lidocaine tape on the reduction of the pain at arteriovenous fistula puncture in hemodialysis patients: A multicentre study.

[12.1. Reporting by Investigators and Subinvestigators 16](#_Toc480461272)

[12.2. Reporting by the Principal Investigator 16](#_Toc480461273)

[13. Definitions of Endpoints **エラー! ブックマークが定義されていません。**](#_Toc480461274)

[13.1. Primary Endpoint **エラー! ブックマークが定義されていません。**](#_Toc480461275)

[13.2. Secondary Endpoint 17](#_Toc480461276)

[14. Statistical Discussion **エラー! ブックマークが定義されていません。**](#_Toc480461277)

[15. Monitoring **エラー! ブックマークが定義されていません。**](#_Toc480461278)

[15.1. Conduct of Monitoring 19](#_Toc480461279)

[15.2. Actual Monitoring Procedure 19](#_Toc480461280)

[15.3. Matters to be Monitored 20](#_Toc480461281)

[16. Ethical Matters **エラー! ブックマークが定義されていません。**](#_Toc480461282)

[17. Handling of Personal Information エラー! ブックマークが定義されていません。](#_Toc480461283)

18. Study Costs

[18.1. Source of Funding and Financial Relationships 22](#_Toc480461284)

[18.2. Costs Associated with the Study 22](#_Toc480461285)

[18.3. Compensation for Health Damage 22](#_Toc480461286)

[19. Deviations from the Protocol **エラー! ブックマークが定義されていません。**](#_Toc480461287)

[19.1. Deviations from or Changes to the Study Protocol 22](#_Toc480461288)

[19.2. Revisions to the Study Protocol 23](#_Toc480461289)

[20. Termination or Early Completion of the Study 23](#_Toc480461290)

[20.1. Completion of the Study 23](#_Toc480461291)

[20.2. Early Termination of the Study 23](#_Toc480461292)

[21. Handling of Materials Associated with Study Materials 24](#_Toc480461293)

[22. Ownership of Study Results and Publication of Effects 24](#_Toc480461294)

[23. Study Organization **エラー! ブックマークが定義されていません。**](#_Toc480461295)

[23.1. Study Sites **エラー! ブックマークが定義されていません。**](#_Toc480461296)

[23.2. Principal Investigator **エラー! ブックマークが定義されていません。**](#_Toc480461297)

[23.3. Study Coordinator **エラー! ブックマークが定義されていません。**](#_Toc480461298)

[23.4. Statistical Analysis Manager 25](#_Toc480461299)

[23.5. Data Center and Data Manager 25](#_Toc480461300)

[23.6. Monitoring **エラー! ブックマークが定義されていません。**](#_Toc480461301)

[24. Support Desk **エラー! ブックマークが定義されていません。**](#_Toc480461302)

[25. References **エラー! ブックマークが定義されていません。**](#_Toc480461303)

1. **Purpose**

The purpose of this study is to carry out a positive-control, two-treatment, two-period crossover trial of the analgesic effect of lidocaine/propitocaine cream (brand name: EMLA Cream) compared with that of lidocaine tape (brand name: Youpatch Tape) during arteriovenous fistula puncture in chronic maintenance hemodialysis patients.

1. **Background and Scientific Rationale**

## Background

Pain during arteriovenous fistula puncture is a major reason for diminished quality of life (QOL) in chronic maintenance hemodialysis patients, and in Japan, where few patients receive kidney transplants, the unavoidable necessity of long-term maintenance dialysis after the start of hemodialysis makes it a compelling issue.

Efforts have been made to relieve pain during arteriovenous fistula puncture by applying lidocaine tape to the puncture site, but poor skin penetration means that in many cases its anesthetic effect is insufficient.^1)^ Because lidocaine/propitocaine cream penetrates the skin well, providing a good anesthetic effect, since its approval in Sweden in 1984 it has come to be widely used worldwide, and has currently been approved in more than 80 countries, where it is used for a variety of indications such as pain relief during injections and intravenous catheter placement and minor skin operations, as well as for children.^2) – 14)^ In Japan, it was approved in January 2012 for use as pain relief during skin laser irradiation therapy, and was launched on the market in May that year. In June 2015, it was also approved for use as pain relief during injections and intravenous catheter placement, since when EMLA Cream has been used to relieve pain during arteriovenous fistula puncture in chronic maintenance hemodialysis patients. However, the analgesic effect of lidocaine/propitocaine cream during arteriovenous fistula puncture in chronic maintenance hemodialysis patients has yet to be fully investigated, including overseas, and it is unclear whether or not its analgesic effect is superior to that of the lidocaine tape that has conventionally been used. This study (a multicenter, joint, nonblinded, nonrandomized, positive-controlled, two-treatment, two-period crossover trial) is a trial of the superiority of the analgesic effect during arteriovenous fistula puncture in chronic maintenance hemodialysis patients of lidocaine/propitocaine cream compared with lidocaine tape.

## Scientific Rationale for the Study

As most cutaneous nerve endings are located in the dermis, topical local anesthetics must pass through the stratum corneum to the dermis to exert an anesthetic effect. The stratum corneum has a structure consisting of layers of corneocytes, with intercellular lipids between these corneocytes acting as a barrier to water-soluble substances. To ensure that local anesthetics can pass through the stratum corneum and reach the dermis, formulations must therefore contain high concentrations of hydrophobic local anesthetics in the emulsified fraction.

Lidocaine/propitocaine cream utilizes the property that when lidocaine and propitocaine, both of which are solids at room temperature, are mixed in equimolar amounts their melting points decrease and they become liquid at room temperature.^15)^ This means that less solvent (oil) need be added, enabling the production of a formulation containing a high concentration of anesthetic in the emulsified fraction.^16)^ These modifications to the formulation should give lidocaine/propitocaine cream excellent skin penetration providing an adequate anesthetic effect, and data confirming its outstanding effectiveness as an anesthetic in clinical practice have been reported, mainly in the fields of dermatology, pediatrics, and anesthesiology.^2)–14)^ However, few studies providing high-level evidence have been conducted of its analgesic effect during arteriovenous fistula puncture in chronic maintenance hemodialysis patients, with only one overseas randomized comparative trial reporting that lidocaine/propitocaine cream has a more effective analgesic effect than placebo or cold spray.^17)^ Although lidocaine/propitocaine cream is thus expected to provide effective pain relief during arteriovenous fistula puncture in chronic maintenance hemodialysis patients, more evidence must be obtained. No randomized trial has previously been conducted to compare the analgesic effect of conventional lidocaine tape and lidocaine/propitocaine cream during arteriovenous fistula puncture. The present study is a superiority trial designed as a positive-control randomized comparative trial to evaluate the analgesic effect of lidocaine/propitocaine cream compared with lidocaine tape as a comparative control, with the objective of demonstrating whether lidocaine/propitocaine cream has a superior analgesic effect during arteriovenous fistula puncture than does lidocaine tape, or whether the reverse is true.

1. **Drug Information**

Overview of Investigational Drugs

Two investigational drugs will be used: the test drug [lidocaine/propitocaine cream (brand name: EMLA Cream)] and the control drug [lidocaine tape (brand name: Youpatch Tape)]. The test drug is approved for pain relief during injection needle/ pain relief during injections and intravenous catheter placement, and the control drug is approved for pain relief during intravenous catheter placement. Their use for pain relief during arteriovenous fistula puncture is covered by health insurance.

Test drug: Lidocaine/propitocaine cream (brand name: EMLA Cream)

Control drug: Lidocaine tape (brand name: Youpatch Tape)

Composition of test drug [lidocaine/propitocaine cream (brand name: EMLA Cream)]

| Content of the active principles (in 1 g) | JP Lidocaine 25 mg  Propitocaine 25 mg |
| --- | --- |
| Excipients | Polyoxyethylene hydrogenated castor oil, carbomer, pH regulator |

Composition and properties of control drug [lidocaine tape (brand name: Youpatch Tape)]

| Content of the active principle | 1 sheet (paste 180 mg) contains JP lidocaine 18 mg |
| --- | --- |
| Excipients | Styrene-isoprene-styrene-block copolymer, cycloaliphatic saturated hydrocarbon resin, liquid paraffin, one other component |
| Properties | Transdermal patch consisting of a colorless, semitransparent paste on a light brown to brown, flexible fabric support and liner |
| Size | 30.5 mm × 50.0 mm |

Dosage and Administration of Investigational Drugs

Test drug [lidocaine/propitocaine cream (brand name: EMLA Cream)]: 1 g of the agent is applied to a single location at the intended puncture site using special fixation tape 1 h before arteriovenous fistula puncture. After the agent has been left in place for 1 h, the tape is removed and the agent is wiped off. Vascular puncture is performed after thorough cleaning and disinfection.

Control drug [lidocaine tape (brand name: Youpatch Tape)]: 1 sheet of the agent is applied to a single location at the intended puncture site 30 min before arteriovenous fistula puncture. The sheet is removed after it has been left in place for 30 min. Vascular puncture is performed after thorough disinfection.

1. **Subjects**

Chronic maintenance hemodialysis patients aged ≥20 years who request topical drug use for pain relief during arteriovenous fistula puncture.

The pain score during arteriovenous fistula puncture is evaluated using a visual analog scale (VAS).

1. **Eligibility Criteria**

## Selection Criteria

1. Chronic maintenance hemodialysis patients undergoing hemodialysis 3 times a week
2. Age ≥20 years
3. Using an arteriovenous fistula (autologous vessels) for vascular access for hemodialysis
4. Informed consent provided voluntarily by the subject himself or herself in writing after a full explanation of study participation

Patients who meet conditions 1)–4) above who request the use of a topical drug for pain relief during arteriovenous fistula puncture

- 1. Exclusion Criteria

1. Allergy to local anesthetic
2. History of contact dermatitis in reaction to a topical drug
3. Serious liver disease [AST (GOT) or ALT (GPT) ≥100 IU/L in most recent regular blood test]
4. Methemoglobinemia
5. Porphyria
6. Pregnancy or lactation
7. Skin disorder at puncture site
8. Serious sensory disorder
9. Participation in another clinical study (clinical trial) within 3 months prior to the start of investigational drug administration
10. Considered by the Principal Investigator or another investigator to be ineligible as a study subject

[Rationale] 1)–6) For reasons of safety, 7)–10) for reasons of the effect on efficacy analysis or safety

1. **Registration and Allocation**

## Patient Registration Procedure

1. The Principal Investigator or another investigator obtains written consent from patients who meet the eligibility criteria.
2. Patient registration (using the central registration method) and randomization are conducted using a cloud–based allocation service system (Iruka System Co., Ltd., Tokyo). The results of this allocation are automatically sent to the doctor who registered the patient.
3. The allocation history for the entire study is managed by a person with no involvement in patient enrollment, the interventions, or statistical analysis.
4. Withdrawal of consent, discontinuation, dropping out, and other such occurrences are immediately reported to the Study Coordinator.

## Allocation Method and Allocation Adjustment Factors

Subjects are randomly allocated to treatment groups by the Study Coordinator at the time they are registered as study participants. To prevent any major bias in (1) age, (2) sex, (3) subjective symptoms, or other factors in the process randomization, the minimization method is used with these factors as adjustment factors.

1. **Study Design**

## Content of Crossover Study

[figure not shown]

| 介入I期（1週間） | Period I (1 week) |
| --- | --- |
| 介入II期（1週間） | Period II (1 week) |
| 同意取得 | Consent obtained |
| 医薬品使用前検査 | Tests prior to investigational drug use |
| 適格性判断 | Eligibility determination |
| 割付け | Allocation |
| 前観察期（1週間） | Period 0 (measurement of baseline 1) (1 week) |
| 被験医薬品毎透析前 | Test drug use (before each dialysis procedure) |
| 対象医薬品毎透析前 | Control drug use ( before each dialysis procedure) |
| 休薬期間（1週間） | Wash-out period (1 week) |

(1) Written consent is obtained from the subject.

（2） Tests prior to investigational drug use are conducted, and eligibility for enrollment in the study (selection criteria/exclusion criteria) is confirmed.

(3) Subjects determined to be eligible as a result of the tests before investigational drug use are randomly allocated into two groups (Group A and Group B). Those in Group A use the test drug (EMLA) followed by the control drug (Youpatch), and those in Group B use the control drug (Youpatch) followed by the test drug (EMLA).

(4) In Period0 (1 week), pain is evaluated during arteriovenous fistula puncture using a visual analog scale (VAS) on all three occasions dialysis is performed from the start of the week to the weekend (Monday, Wednesday, and Friday or Tuesday, Thursday, and Saturday) without the use of the investigational drugs. The pain score (VAS) during arteriovenous fistula puncture during the final dialysis of that week is defined as the Baseline 1 pain score during arteriovenous fistula puncture (without drug use) [VAS (Group A pre-intervention Period I value) and VAS (Group B pre-intervention Period I value]. Health-related quality of life (QOL) is assessed using the SF36 (Acute Version: 1-week recall period) after the final dialysis of that week (Friday or Saturday).

（5）In Period I (1 week), the allocated investigational drug [Group A: test drug (EMLA); Group B: control drug (Youpatch)] is used on all three occasions dialysis is performed from the start of the week to the weekend (Monday, Wednesday, and Friday or Tuesday, Thursday, and Saturday). The pain score is evaluated by VAS after arteriovenous puncture on each occasion dialysis is performed. The mean pain score (VAS) during these three arteriovenous fistula punctures is defined as the pain score during arteriovenous fistula puncture when the drug concerned is used [Group A: VAS (Group A EMLA); Group B: VAS (Group B Youpatch)]. In addition, ΔVAS (Group A EMLA) [= VAS (Group A EMLA) – VAS (Group A pre-Intervention Period I score)] is defined as the total effect of EMLA Cream in Group A, and ΔVAS (Group B Youpatch) [= VAS (Group B Youpatch) – VAS (Group B pre-Intervention Period I score)] is defined as the total effect of Youpatch Tape in Group B. Health-related quality of life (QOL) is assessed using the SF36 (Acute Version: 1-week recall period) after the final dialysis of that week (Friday or Saturday).

(6) In the wash-out period (1 week), pain during arteriovenous fistula puncture is evaluated by VAS on all three occasions dialysis is performed from the start of the week to the weekend (Monday, Wednesday, and Friday or Tuesday, Thursday, and Saturday) without the use of the investigational drugs. The pain score (VAS) during arteriovenous fistula puncture during the final dialysis of that week is defined as the Baseline 2 pain score during arteriovenous fistula puncture (without drug use) [VAS (Group A pre-Intervention Period II score) and VAS (Group B pre-Intervention Period II score]. Health-related quality of life (QOL) is assessed using the SF36 (Acute Version: 1-week recall period) after the final dialysis of that week (Friday or Saturday).

(7) In Period II (1 week), use the allocated investigational drug [Group A: control drug (Youpatch); Group B: test drug (EMLA)] on all three occasions dialysis is performed from the start of the week to the weekend (Monday, Wednesday, and Friday or Tuesday, Thursday, and Saturday). The pain score is evaluated by VAS after arteriovenous puncture on each occasion dialysis is performed. The mean pain score (VAS) during these three arteriovenous fistula punctures is defined as the pain score during arteriovenous fistula puncture when the drug concerned is used [Group A: VAS (Group A Youpatch); Group B: VAS (Group B EMLA)]. In addition, ΔVAS (Group A Youpatch) [= VAS (Group A Youpatch) – VAS (Group A pre-Period II score)] is defined as the total effect of Youpatch Tape in Group A, and ΔVAS (Group B EMLA) [= VAS (Group B EMLA) – VAS (Group B pre- Period II score)] is defined as the total effect of EMLA in Group B. Health-related quality of life (QOL) is assessed using the SF36 (Acute Version: 1-week recall period) after the final dialysis of that week (Friday or Saturday).

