## 8.2. Schedule for Monitoring, Testing, and Reporting

| Period  Parameter | Consent obtained – determination of eligibility for study enrollment | Pre-observation period (1 week) | Period I (1 week) | Wash out (1 week) | Period II (1 week) |
| --- | --- | --- | --- | --- | --- |
| Explanation of study/obtaining consent | ○ |  |  |  |  |
| Investigation of patient characteristics | ○ |  |  |  |  |
| Examination by doctor | ○ |  |  |  |  |
| Height, weight | ○ |  |  |  |  |
| Temperature, blood pressure, heart rate | ○ | ○ | ○ | ○ | ○ |
| Pain score during arteriovenous fistula puncture measured by VAS (on every occasion dialysis is performed) |  | ○ | ○ | ○ | ○ |
| Health-related QOL measured using the SF36 (acute version) (after final dialysis in that period) |  | ○ | ○ | ○ | ○ |
| Check made for adverse events caused by the interventional drug |  |  | ○ | ○ | ○ |
|  | | | | | |

8.3. Specimen Storage and Use of Specimens by Other Institutions, Etc.

Materials concerning this study stored by the study sites and the Principal Investigator (including records of subject observations, test data, Ethics Committee screening records, and subject consent forms) shall be retained until a date 5 years from the date of completion of the study as a whole or 3 years from the date of final publication of the results of the study, whichever is the later. After the end of the retention period, they are to be disposed of appropriately (shredded or burned).

Specimens such as blood and urine samples will not be collected in this study.

1. **Target Enrollment and Study Period**
   1. Target Enrollment

The target number of applications in this hospital is 20 patients.

The total number of subjects to be enrolled in the study as a whole is 68 patients.

(The study as a whole will include Kanazawa Medical University Hospital, Keiju Medical Center, Anamizu General Hospital, and others)

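### The sequence is allocated and disclosed before the drug-free baseline week of an open-label trial; allocating after Period 0 would protect Baseline 1 at almost no cost

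*Protocol*

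**What the plan says.** The order of events is fixed in the numbered steps of section 7.1 (Content of Crossover Study). After consent and eligibility tests, step (3) reads: "Subjects determined to be eligible as a result of the tests before investigational drug use are randomly allocated into two groups". Step (4) follows: "In Period0 (1 week), pain is evaluated during arteriovenous fistula puncture using a visual analog scale (VAS) on all three occasions dialysis is performed", with no study drug in use. The VAS score "during the final dialysis of that week is defined as the Baseline 1 pain score during arteriovenous fistula puncture (without drug use".

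Section 6.2 (Allocation Method and Allocation Adjustment Factors) agrees on the timing: "Subjects are randomly allocated to treatment groups by the Study Coordinator at the time they are registered as study participants". On disclosure, section 6.1 (Patient Registration Procedure) says: "The results of this allocation are automatically sent to the doctor who registered the patient". The Background section describes "a multicenter, joint, nonblinded, nonrandomized, positive-controlled, two-treatment, two-period crossover trial". (The word nonrandomized there conflicts with sections 6.1, 6.2 and 7.1. That is a separate matter, and this point takes the trial as randomized.)

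Minimization is used: "To prevent any major bias in (1) age, (2) sex, (3) subjective symptoms, or other factors". The third factor is not defined. In the section 8.2 schedule, the row "Pain score during arteriovenous fistula puncture measured by VAS (on every occasion dialysis is performed" is marked from the pre-observation week onwards and is blank for the consent and eligibility stage.

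Steps (5) and (7) of section 7.1 define the effect of each drug as the mean on-drug VAS of the period minus the baseline before that period. Section 14 builds the primary test from these differences.

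**The concern.** Period 0 exists to supply an untreated reference value. That value is a subjective rating, taken once, in a trial without blinding. Because allocation comes first, the rating is made when the registering doctor already holds the sequence and the patient may have been told it. If expecting one drug rather than the other next week changes how patients rate puncture pain, or how staff frame the question, Baseline 1 would move differently in Groups A and B. The endpoint subtracts Baseline 1, so any such movement passes into the treatment comparison. The Period 0 SF36 has the same exposure, because section 14 analyses QOL in the same way as the primary endpoint.

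Two lesser consequences follow from the same ordering. The study's own pain score does not yet exist when minimization is run. Anyone who withdraws during Period 0 is already randomized although no study drug has been used.

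**Working it through.** **Does the protocol hold the sequence back?** Three places bear on it.

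- Sections 6.2 and 7.1 put allocation at registration, one step before Period 0. I rely on the numbered text, as the flow figure was not available to me.
- Section 6.1 has the allocation history managed by someone outside enrolment, intervention and analysis. That guards the overall list; the same section still sends each patient's result to the registering doctor.
- No section delays release until Period I.

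**Where Baseline 1 enters the estimate.** Write V for the mean on-drug VAS of a period, B1 and B2 for the two baselines, and A and B for the sequence groups. From sections 7.1 and 14:

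- D_A = (V_A1 − B1_A) − (V_A2 − B2_A)
- D_B = (V_B1 − B1_B) − (V_B2 − B2_B)

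Section 14 gives D_A − D_B = 2(T_I − T_C), so the treatment estimate is

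(D_A − D_B)/2 = ½[(V_A1 − V_A2) − (V_B1 − V_B2)] − ½(B1_A − B1_B) + ½(B2_A − B2_B).

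If knowledge of the sequence raises B1 in Group A relative to Group B by δ and nothing else moves, the estimate changes by −δ/2. In the carryover contrast S_A − S_B the term is −(B1_A − B1_B), so the shift enters there in full and could be read as carryover.

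If instead Group A has a stable pain level c mm higher at every reading, c cancels within each V − B difference. A stable imbalance between sequences therefore does not bias the estimate.

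**The plan's own figures.** Inputs from section 14: difference 10 mm, intra-individual SD 20 mm, two-sided α 5%, power 80%. For a 2×2 crossover,

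N = 2 × 20² × (1.960 + 0.842)² / 10² = 62.8 in total.

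The plan states 62 (31 per group), which agrees within rounding. The standard error of the treatment estimate with 62 patients is √(2 × 20²/62) = √12.90 = 3.59 mm.

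**Sensitivity to δ.** The values of δ are assumed; the protocol gives none. The last column is the two-sided type I error of a nominal 5% test, Φ(b/SE − 1.96) + Φ(−b/SE − 1.96), with b = δ/2.

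| Assumed δ (mm) | Shift b = δ/2 (mm) | b as share of 10 mm | b/SE | Type I error |
| --- | --- | --- | --- | --- |
| 2 | 1 | 10% | 0.28 | 5.9% |
| 5 | 2.5 | 25% | 0.70 | 10.7% |
| 10 | 5 | 50% | 1.39 | 28.5% |

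**The case against.** The order of events and the algebra are not in dispute. The strongest case against concerns what follows from them.

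- **The patient's knowledge is inferred.** A reader might conclude that Baseline 1 is rated by patients who know their sequence. The protocol says only that the doctor receives it. In a nonblinded trial nothing stops the patient being told, but no section says this happens before Period 0. This stands: the exposure is possible, not documented.
- **δ has no support.** Every patient receives both drugs, so knowing the sequence means knowing only which comes first. Nothing in the documents shows that this would shift a drug-free rating. This stands: the table cannot be read as an expected bias.
- **The minimization factor may not be empty.** A reader might infer that no symptom information exists at allocation. The section 8.1 list includes complications and history of the current condition and is open-ended, and section 8.2 adds a doctor's examination. The undefined factor could come from these. Only the VAS is shown to be unavailable.
- **Pain balance matters little here.** A reader might infer that an imbalance in pain would bias the primary result. Stable differences cancel, as shown, and random allocation balances pain in expectation anyway. Only the extra balance that minimization would force is lost.
- **Period 0 losses may be few.** It is one drug-free week, enrolment of 68 already allows for dropout, and handling such patients in the Full Analysis Set may be left to the SAP. This too stands, so the point is a side benefit.
- **The remedy is partial.** Baseline 2 and all on-drug ratings remain open-label whatever is done. This is correct and limits the gain.

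None of this gives a reason to allocate before Period 0. That week is the same in both groups, so nothing in it needs the sequence.

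**Conclusion.** The point holds as an avoidable exposure of one quantity in the primary endpoint. Allocation and disclosure come before the baseline week, and Baseline 1 carries a weight of one half in the treatment estimate. Any sequence-related shift therefore enters at δ/2: 1 to 5 mm for assumed δ of 2 to 10 mm, against a planned 10 mm. This assumes that δ acts on Baseline 1 alone; a shift common to all readings would cancel. The type I error figures also take the planning SD of 20 mm and 62 evaluable patients as given.

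The documents do not show that δ differs from zero, that patients know the sequence in Period 0, or that the trial's result would be biased. The missing VAS at minimization is a minor weakness. The ordering is a design choice that can be improved cheaply and does not invalidate the analysis. The planned sample size is unaffected.

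**What to change.** In sections 6.1, 6.2 and 7.1, separate registration from allocation. Consent, eligibility and registration stay where they are. The cloud allocation is run, and its result released, only after the VAS and SF36 of the final Period 0 dialysis have been recorded.

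In section 6.2, replace the undefined symptom factor and the open-ended reference to other factors with the Period 0 VAS, alongside age and sex. State whether this is the mean of the three ratings or the final-session score that defines Baseline 1, and give the categories. This is the secondary part of the change.

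Patients who withdraw in Period 0 would then not enter the randomized set.

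The cost is one later log-in per patient and a small change to the allocation set-up. If the weeks run consecutively, the log-in falls between Friday and Monday, or Saturday and Tuesday. Sites learn the sequence a week later; both drugs are commercial products, so this should be manageable. No visit or patient is added. The protocol should acknowledge that Baseline 2 and the on-drug ratings remain open-label.

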**Method of Analysis of Primary Endpoint**

The primary endpoint is analyzed by the standard statistical procedures^18)^ for a two-group, two-period crossover study.

Total effect of EMLA Cream in Group A (E_A1I_) = ΔVAS (Group A EMLA)

Total effect Youpatch Tape in Group A (E_A2C_) = ΔVAS (Group A Youpatch)

Total effect of EMLA Cream in Group B (E_B2I_) = ΔVAS (Group B EMLA)

Total effect Youpatch Tape in Group B (E_B1C_) = ΔVAS (Group B Youpatch)

Crossover design analysis

|  | Period I | Period II | Difference in effects | Sum of effects |
| --- | --- | --- | --- | --- |
| Group A | EMLA  E_A1I_ = T_I_ + P_I_ + TP_A_ | Youpatch  E_A2C_ = T_C_ + P_2_ + TP_A_ | D_A(1 – 2)_ = E_A1I_ – E_A2C_  = (T_1_ – T_C_） + (P_1_ – P_2_) | S_A(1 + 2)_ = E_A1I_ + E_A2C_ = (T_I_ + T_C_) + (P_1_ + P_2_) + 2TP_A_ |
| Group B | Youpatch  E_B1C_ = T_C_ + P_1_ + TP_B_ | EMLA  E_B2I_ = T_I_ + P_2_ + TP_B_ | D_B(1 – 2)_ = E_B1C_ – E_B2I_  = [ – (T_I_ – T_C_)] + (P_1_ – P_2_) | S_B(1 + 2)_ = E_B1C_ + E_B2I_ = (T_I_ + T_C_) + (P_1_ + P_2_) + 2TP_B_ |

E: Total effect: T: treatment effect; P: period effect; TP: treatment–period interaction effects (or allocation effects or carryover effects).

Subscripts: I: EMLA Cream; C: Youpatch Tape; 1: Intervention Period I; 2: Intervention Period II; A: Group A; B: Group B.

(1) Analysis of period effect

D_A(1 – 2)_ – ( – D_B(1 – 2)_) = D_A(1 – 2)_ – D_B(2 – 1)_ = 2(P_1_ – P_2_)

Test whether or not this is 0 by comparing D_A(1 – 2)_ and D_B(2 – 1)_ using an unpaired t-test, and if the difference is not significant the period effect may be ignored.

(2) Analysis of carryover effect

S_A(1 + 2)_ – S_B(1 + 2)_ = 2(TP_A_ – TP_B_)

Test whether or not this is 0 by comparing S_A(1 + 2)_ and S_B(1 + 2)_ using an unpaired t-test, and if the difference is not significant the carryover effect may be ignored.

(3) Analysis of treatment–period interaction effects (or allocation effects or carryover effects)

D_A(1 – 2)_ – D_B(1 – 2)_ = 2(T_I_ – T_C_)

Compare D_A(1 – 2)_ and D_B(1 – 2)_ using an unpaired t-test, and test the difference between the treatment effect of EMLA Cream (T_I_) and that of Youpatch Tape (T_C_) for significance.

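### The primary variable subtracts a single drug-free reading from a three-session on-drug mean, which discards recorded baseline data and costs precision in a contrast that is already within-patient

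*Protocol*

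**What the plan says.** Protocol Section 7.1 (Content of Crossover Study) has VAS taken in Period 0 and in the wash-out, both without drug, "on all three occasions dialysis is performed from the start of the week to the weekend". From each of those weeks one reading is kept. For Period 0: "The pain score (VAS) during arteriovenous fistula puncture during the final dialysis of that week is defined as the Baseline 1 pain score". For the wash-out, the reading "during the final dialysis of that week is defined as the Baseline 2 pain score".

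The on-drug weeks are handled differently: "The mean pain score (VAS) during these three arteriovenous fistula punctures is defined as the pain score during arteriovenous fistula puncture". ΔVAS is the on-drug mean minus the baseline of the same period, so the Period II value subtracts Baseline 2.

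Section 14 (Method of Analysis of Primary Endpoint) carries this into the test: "Total effect of EMLA Cream in Group A (E_A1I_) = ΔVAS (Group A EMLA"), and similarly for the other three cells. These effects form D_A and D_B (Period I minus Period II), which are compared by an unpaired t-test. No reason is given for using one session. SF36 is to be analysed in the same way.

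**The concern.** Two features of this definition deserve attention.

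First, four of the six drug-free readings per patient are unused in the primary variable, and the two that remain are single VAS ratings set against means of three. D is a difference between two periods in the same patient, so stable differences between patients have already cancelled. Subtracting a period baseline can help only if a drug-free week shares something with the on-drug week that follows and not with the other weeks. Otherwise it adds the baseline's own error, with a coefficient fixed at 1.

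Second, Baseline 2 is taken after the Period I drug, in a trial that Section 2.1 describes as not blinded. A residual or expectation effect on that reading can therefore enter the EMLA versus Youpatch contrast.

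At stake are the width of the primary confidence interval and the chance of detecting differences below the planned 10 mm.

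**Working it through.** **Inputs.** From Section 14: difference 10 mm, intra-individual SD in VAS improvement 20 mm, two-sided 5%, 80% power, 31 per group before dropout and 34 after. From Section 7.1: one session per baseline, three per on-drug score. Not in the protocol, hence assumed: the session variance s² and the correlation between sessions.

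**The plan's own figure.** For a two-period crossover, n per sequence = (1.96 + 0.84)² × 20² / 10² = 7.849 × 4 = 31.4, or 62.8 in total. The stated 31 and 62 reproduce to rounding. Power at 31 per group is 79.5% by the normal approximation and 78.2% by the t distribution. Dropout of 5% to 10% gives 33 to 35, consistent with 34.

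**Variance of D.** Let p be the share of within-patient variance common to sessions of the same week. A three-session mean has variance m = p s² + (1 − p)s²/3; a single session has s².

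- As written: Var(D) = 2(m + s²)
- Three-session means for both baselines: 4m
- Three-session Baseline 1, single-session Baseline 2: 3m + s²
- On-drug means, no subtraction: 2m

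Anchor the as-written case at SD(ΔVAS) = 20 mm, so SD(D) = √2 × 20 = 28.3 mm (with p = 0, 4s²/3 = 400 gives s = 17.3 mm). Then SE = 0.5 × 28.3 × √(2/31) = 3.59 mm, and with t = 2.00 on 60 df the half-width is 7.2 mm. The other rows scale by the square root of the variance ratio.

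| Primary variable | Var(D)/s², p = 0 | Half-width | Var(D)/s², p = 0.5 | Half-width |
|---|---|---|---|---|
| As written | 2.67 | ±7.2 mm | 3.33 | ±7.2 mm |
| Three-session Baseline 1 only | 2.00 | ±6.2 mm | 3.00 | ±6.8 mm |
| Both baselines three-session | 1.33 | ±5.1 mm | 2.67 | ±6.4 mm |
| On-drug means | 0.67 | ±3.6 mm | 1.33 | ±4.5 mm |

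For p = 0, 0.25, 0.5 and 0.75 the variance ratio of as written to three-session baselines is 2.0, 1.5, 1.25 and 1.1. Against no subtraction it is 4.0, 3.0, 2.5 and 2.2.

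**Serial correlation.** With half independent noise and half autocorrelated error, the ratio to three-session baselines is 1.35 to 1.49. With purely autocorrelated error and no independent noise, it falls to 0.93 and 0.81 at correlations of 0.7 and 0.9 between adjacent sessions. At 0.9 the ratio to no subtraction also falls just below 1 (0.94).

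**Covariate with estimated slope.** With D_Y the on-drug difference and D_B the drug-free difference, the residual variance is Var(D_Y) − Cov(D_Y, D_B)²/Var(D_B). In the independent and week-shared cases the covariance is zero, so the result equals the on-drug row apart from one degree of freedom. In the extreme 0.9 case, with three-session means, both variances are 0.863 s² and the subtracted version has 0.999 s². The covariance is therefore (2 × 0.863 − 0.999)/2 = 0.364, leaving 0.863 − 0.364²/0.863 = 0.71 s², against 0.81 s² as written.

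**Baseline 2.** Let λ_E and λ_C be residual effects at the last wash-out session after EMLA and after tape. If they are gone by Period II, D_A shifts by λ_E and D_B by λ_C, and the estimate shifts by (λ_E − λ_C)/2. For illustration, λ_E = −4 and λ_C = −1 turn a true −10 mm into −11.5 mm. If the effects persist unchanged into Period II, the subtraction cancels them (−10.0 mm), while on-drug means alone would give −8.5 mm.

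**The case against.** The 20 mm SD is stated for VAS improvement, which is the quantity analysed, so it may already contain the baseline noise. A reader might infer that the trial is underpowered or its sample size wrong; the protocol does not support that, since the stated number reproduces from its own inputs. This objection stands and limits the point to efficiency.

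A reader might also take the fourfold variance, or the matching power gain (from 78% to 97% with three-session baselines and above 99.9% with on-drug means), as the expected size. Those figures require fully independent sessions and are upper bounds within the independent and week-shared cases.

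It is tempting to say that Baseline 2 biases the comparison. That holds only if a residual effect differs by drug, is present at the last wash-out session and has gone by Period II. The protocol has no data on this, and under persistent carryover the subtraction helps. The last-session rule is also defensible for Baseline 2, being the reading furthest from Period I drug use; averaging the wash-out sessions improves precision but does not remove its post-treatment nature. That defence does not extend to Baseline 1, which precedes any study drug.

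The one-against-three mismatch does not carry over to SF36, which is measured once per period. Finally, ΔVAS has a use in the carryover test, because the sum S keeps between-patient variation that a baseline can remove. It can stay there without being the variable for the treatment test.

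**Conclusion.** The point holds as a loss of efficiency in the definition of the primary variable. As written, the variance of the treatment contrast is about 1.1 to 2.0 times that with three-session baselines and 2.2 to 4.0 times that with no subtraction, over independent and week-shared error structures. The first comparison reverses only under strong serial correlation with no independent measurement error, which is hard to defend for single VAS ratings. The half-widths in millimetres assume that 20 mm is the SD of ΔVAS as defined and that 31 patients per sequence are analysed. The planned test remains usable. Dependence on Baseline 2 is a conditional risk of either sign, best handled by sensitivity analysis.

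**What to change.** For the treatment test, compare D of the three-session on-drug means between sequences, with the drug-free difference as a covariate whose slope is estimated. That difference is the mean of the three Period 0 readings minus the wash-out value, taken as a three-session mean, or as the final session if carryover is a concern.

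At minimum, define Baseline 1 as the mean of the three Period 0 sessions.

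Keep two sensitivity analyses: the final-session ΔVAS as now defined, and one that uses no wash-out readings. The second is needed because the covariate still contains post-treatment values. For SF36, only the replacement of subtraction by a covariate applies.

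Cost: wording in Sections 7.1, 13.1 (where the endpoint is defined as a before-and-after improvement) and 14, plus one degree of freedom. No new visits, patients or measurements are needed. The 20 mm planning SD would then describe the sensitivity analysis and be conservative for the primary. The choice should be fixed before outcomes are seen.
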